#### Primary objective

2.1.1

To implement a streamlined process to promote access to a CV risk hospital consultation, through the systematic identification of individuals with elevated CV risk in OM consultations carried out in industrial/manufacturing companies’ workers in the municipality of São João da Madeira.

#### Secondary objectives

2.1.2

Secondary objective 1: To assess the effective referral rate of identified patients with elevated CV risk in OM to the CV risk hospital consultation.Secondary objective 2: To assess the rate of hospital CV risk consults that effectively took place after the referral by the OM physician.Secondary objective 3: To measure the performance of the simplified referral process for a CV risk consultation, through the assessment of therapeutic adherence, and impact on the CV risk profile 12 months after the intervention.Secondary objective 4: To estimate the levels of Lipoprotein (a) in patients.Secondary objective 5: To estimate the prevalence of CV risk factors in workers in the industrial/manufacturing companies in the municipality of São João da Madeira, using the AHA Life's 8 system.Secondary objective 6: To assess the effective referral rate of patients to the primary care consultation.Secondary objective 7: To assess the effective application of the implementation strategies in the CARDIOGAP + project.

#### Implementation science framework

2.1.3

This protocol is informed by the RE-AIM framework (Reach, Effectiveness, Adoption, Implementation, Maintenance), used to plan and evaluate pragmatic, real-world health system interventions. Primary and secondary objectives relate to RE-AIM dimensions as follows: Reach is addressed through the proportion of eligible OM attendees identified and screened (secondary objectives 1–2); Effectiveness is addressed through change in CV risk profile at 12 months (secondary objectives 3–4); Adoption is addressed through the referral rate by OM physicians and participating companies (secondary objectives 1 and 6); Implementation is addressed through fidelity to the referral protocol and consultation attendance (secondary objectives 2 and 7); and Maintenance, while outside the 18-month observation window of this pilot, will be discussed qualitatively as a direction for future, longer-term evaluation.

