#### Statistical methods

2.3.1

To address the multifaceted endpoints of this study (Table 3), a combination of statistical techniques will be employed. Descriptive statistics will be calculated to assess various CV risk factors. Continuous variables will be summarized using n, mean, median, standard deviation, minimum, maximum and 25th and 75th percentiles. Categorical variables will be summarized using frequency counts and percentages. Missing data will be reported using frequency counts and percentages and assessed for pattern and extent; where data are judged to be missing at random, multiple imputation will be used as the primary approach. Outliers will be identified using standard distributional criteria, and treated in consideration of their impact on the analysis.

**Table 3 T3:** Cardiogap + endpoints.

Endpoint Description
1. Proportion (%) of patients who meet the follow-up criteria for CV risk hospital consultation identified in OM consultation: Descriptive statistics will be used to calculate the percentage of patients who meet the follow-up criteria for CV risk hospital consultation over all patients attending OM consultations.
2. Proportion (%) of High CV risk individuals identified in OM consultation: Descriptive statistics will be used to calculate the percentage of High CV patients over all patients attending OM consultations.
3. Proportion (%) of Very High CV risk individuals identified in OM consultation: Descriptive statistics will be used to calculate the percentage of Very High CV patients over all patients attending OM consultations.
4. Proportion (%) of patients referred to Hospital CV Risk Consultation, overall and stratified by risk category: Descriptive statistics will be used to calculate the percentage of patients referred to Hospital CV Risk Consultation, reported (a) over allpatients meeting follow-up criteria, (b) over High CV risk patients only, and (c) over Very High CV risk patients only, identified in OM consultation.
5. Proportion (%) of Hospital CV Risk Consultation Participation after Referral by OM: Descriptive statistics will be used to calculate the percentage of individuals referred from OM consultations who participate in hospital CV risk consultations over all patients referred to hospital consultations.

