### Consent

3.2

The Occupational Safety and Health Technician will provide the informed consent form to the participant on-site and store it alongside the other clinical records. The study coordinator will later collect the consent form, along with the other paper versions of the CRF, and keep it in the ULSEDV. A signed copy will be given to the participant.

Eligible patients may only be included in the study after providing written (witnessed, where required by law or regulation), IRB/EC-approved informed consent, or, if incapable of doing so, after such consent has been provided by a legally acceptable representative of the patient. In cases where the patient's representative gives consent, the patient should be informed about the study to the extent possible given his/her understanding. If the patient is capable of doing so, he/she should assent by personally signing and dating the written informed consent document or a separate assent form. Informed consent must be obtained before any data are collected. The process of obtaining informed consent should be documented in the patient source documents.

Treating physicians or other involved medical professionals will be provided in a separate document a proposed informed consent form that complies with the Declaration of Helsinki principle and regulatory requirements and is considered appropriate for this study.

It's important to note that participation in this study will not result in any alterations to the standard treatment provided to the patients. Therefore, no risks or discomforts are expected for participants due to their involvement in this research. Participation is voluntary and completely free for all individuals involved. Participants have the freedom to withdraw from the project at any time, without any adverse consequences or impact on their care.

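### Reach is described as coverage of Occupational Medicine attendees, but it is mapped to referral and attendance rates that cannot yield it, and its denominator is ambiguous

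*Protocol article*

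**What the plan says.** All references are to the protocol article.

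- **Section 2.1.3 (implementation framework):** "Reach is addressed through the proportion of eligible OM attendees identified and screened", with secondary objectives 1 and 2 given as the source. The same paragraph says "Adoption is addressed through the referral rate by OM physicians and participating companies" (objectives 1 and 6) and "Implementation is addressed through fidelity to the referral protocol and consultation attendance" (objectives 2 and 7).
- **Section 2.1.2:** objective 1 is "To assess the effective referral rate of identified patients with elevated CV risk in OM to the CV risk hospital consultation". Objective 2 is "To assess the rate of hospital CV risk consults that effectively took place after the referral by the OM physician".
- **Sections 2.2.1 and 2.2.1.1:** written consent and willingness and ability to be assessed are listed among the eligibility criteria, beside age 18 to 70 and current employment. Workers who will not or cannot be assessed are the only exclusions.
- **Section 3.2:** "Eligible patients may only be included in the study after providing written" consent, and "Informed consent must be obtained before any data are collected".
- **Table 3:** endpoint 1 is to "calculate the percentage of patients who meet the follow-up criteria for CV risk hospital consultation over all patients attending OM consultations". Endpoints 2 and 3 use the same denominator for the high and very high risk categories.
- **Section 2.2.2:** the precision statement is based on 1000 included persons.
- **Table 2 and section 2.2.5:** consent and willingness are baseline fields, and the technician checks them before the Occupational Medicine (OM) appointment.

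**The concern.** Reach should tell the reader how much of the target workforce the OM route covers. The primary objective is systematic identification of workers at elevated risk, and section 2.4 presents the use of mandatory OM infrastructure as a strength because it screens workers whom primary care often misses. OM attendance is mandatory but study participation is voluntary, so coverage can be lost at consent. Section 2.4 discusses the healthy-worker effect and barriers to hospital attendance, not refusal among OM attendees.

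An analyst who follows the mapping in section 2.1.3 will report a referral or attendance rate under the name Reach. Both can be high even if many workers declined. A pilot meant to inform a larger evaluation would then lack the coverage figure, and a refusal count not kept during enrolment may not be recoverable afterwards.

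**Working it through.** **Step 1. Compare the stated Reach with the objectives mapped to it.**

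| Quantity | Numerator | Denominator |
|---|---|---|
| Reach as described (2.1.3) | attendees identified and screened | eligible OM attendees |
| Secondary objective 1 (2.1.2) | referred patients | patients already identified at elevated risk |
| Secondary objective 2 (2.1.2) | hospital consultations held | referred patients |

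Both objectives start after screening is complete, so a worker who was never screened enters neither ratio. They cannot yield the Reach proportion.

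**Step 2. Look for it among the endpoints.** In Table 3, endpoints 1 to 3 are proportions in risk categories and endpoint 4 is hospital referral. Endpoint 5 is hospital attendance, 6 medication adherence, 7 smoking-cessation attendance and 8 the 12-month change in risk factors. Endpoint 9 is lipoprotein(a), 10 the prevalence of risk factors and 11 referral to the general practitioner. None is a share of attendees screened or enrolled.

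**Step 3. Compare the two uses of the word eligible.** Under section 2.2.1 an eligible worker has consented and is willing to be assessed, so decliners leave the denominator. Under section 3.2 a person is eligible first and consents afterwards, so decliners stay in it. The two uses give different values of Reach whenever anyone declines.

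**Step 4. Reproduce the plan's own figure.** With p = 0.15 and n = 1000 (section 2.2.2), 1.96 × sqrt(0.15 × 0.85 / 1000) = 0.0221, or 2.2 points as stated. It refers to persons included.

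**Step 5. Size of the ambiguity.** The documents give no participation rate, so c = 60% to 90% is an assumption. With 1000 participants the number of attendees is 1000/c. Reach over all attendees is c, with 95% half-width 1.96 × sqrt(c(1−c)/(1000/c)).

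| c | Attendees | Decliners | Half-width (points) | Distance from 100% (points) |
|---|---|---|---|---|
| 90% | 1111 | 111 | 1.8 | 10 |
| 80% | 1250 | 250 | 2.2 | 20 |
| 70% | 1429 | 429 | 2.4 | 30 |
| 60% | 1667 | 667 | 2.4 | 40 |

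The last column is an upper bound, since Reach on the section 2.2.1 reading falls below 100% if some consenting workers are not fully screened.

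**Step 6. Endpoints 1 to 3.** Risk category can be known only for consenting, assessed workers (section 3.2). Let d be the prevalence in decliners minus that in participants, also an assumption. Prevalence over all attendees is c × 15% + (1−c) × (15% + d), so the gap from the participants' 15% is (1−c) × d.

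| c | d = 0 | d = 5 points | d = 10 points | d needed to exceed 2.21 points |
|---|---|---|---|---|
| 90% | 0 | 0.5 | 1.0 | 22.1 |
| 80% | 0 | 1.0 | 2.0 | 11.1 |
| 70% | 0 | 1.5 | 3.0 | 7.4 |
| 60% | 0 | 2.0 | 4.0 | 5.5 |

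At d = 5 points every gap stays below the stated margin.

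**The case against.** The best defence is that section 3.2 speaks of eligible people before consent. On that reading the sentence on Reach already describes coverage, and listing consent among inclusion criteria is ordinary drafting. This stands against a stronger reading that a reader might infer, namely that Reach fails to measure coverage under any reading or is fixed near 100%. The documents do not support that. Even after consent, screening can be incomplete: the risk algorithms in Figure 1 are given for ages 40 and over, HDL may be unavailable in the OM setting, and missing data are expected. The term is ambiguous, not necessarily circular.

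It can also be said that one objective may inform two RE-AIM dimensions, which is true. Sharing is not the fault; the fault is that neither shared objective contains the quantity that Reach names.

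A third defence is that a condensed article leaves participant flow and operational denominators to the full protocol or analysis plan. That would answer a complaint about missing detail. Here the article states a definition and a source that do not match, so a later document would have to correct the text.

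The consent and willingness fields in Table 2 show where refusals could be counted. The article does not say that records of refusals are kept, and no objective or endpoint uses such a count.

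Finally, the wording of endpoints 1 to 3 can be read as shorthand for enrolled patients, in line with section 2.2.2. This largely stands and reduces that part to a wording correction.

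**Conclusion.** The point holds for Reach. As mapped, secondary objectives 1 and 2 cannot produce the proportion that section 2.1.3 describes, no endpoint supplies it, and the denominator has two possible meanings. This follows from the text alone. Its size depends on the participation rate: at an assumed 60% to 90%, the two readings differ by up to 10 to 40 points, well beyond a half-width of 1.8 to 2.4 points.

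For endpoints 1 to 3 the conclusion is limited to wording. A reader might infer that they are biased or cannot be computed. The documents support neither: the proportions can be computed among participants, and any gap to all attendees rests on two assumed quantities and is zero if decliners resemble participants. It would also be wrong to divide the positives among participants by all attendees, since that counts unassessed workers as negative, and nobody proposes it. Endpoints 4 and 5 are not affected, and nothing in the documents says that decliners are refused a referral.

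The change is worth making before or during enrolment. This is a descriptive pilot, and no hypothesis test depends on it.

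**What to change.** 1. In section 2.1.3, define Reach as enrolled and assessed participants divided by all workers aged 18 to 70 who attend OM in the participating companies during the 6-month enrolment phase.
2. Keep an anonymous count of attendees and refusals per company at the inclusion check that already takes place (section 2.2.5, with the consent and willingness fields of Table 2).
3. Link Reach to the primary objective and add it to Table 3 as an endpoint, so that it has a measure of its own.
4. Correct the mapping so that secondary objectives 1 and 2 no longer stand in for Reach. They may remain under Adoption and Implementation.
5. As a minor wording correction, state the denominator of endpoints 1 to 3 as consenting, assessed participants and report the participation rate beside them.

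The cost is one small tally per company and a few reworded lines. Visits, laboratory tests and sample size do not change. The drawback for the sponsor is that the Reach figure may look less favourable than a referral or attendance rate.

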### Study design and setting

2.2

Prospective pilot project for the integration of services, with a pragmatic design. Data collection lasts for 18 months in two distinct phases (Figure 1):
A cross-sectional 6-month intervention phase to enroll patients and operationalize the primary objective and secondary objectives 1, 2 and 5. This is to implement a process to promote the access to cardiovascular risk hospital appointments, through the systematic identification of very high CV risk patients in appointments from Occupational Health carried out on workers from the industrial/manufacturing companies of the municipality of São João da Madeira.A longitudinal, clinical follow-up phase, lasting 12 months, to assess secondary objectives 3 through 6. This is to estimate pharmacological therapy adherence and the impact on cardiovascular risk profile after the intervention above mentioned.

**Figure 1 F1:**
[figure not shown]
Overview of patient participation and data collection. OM: Occupational Medicine; CV: cardiovascular; T0: first hospital consultation; T12: 12-month hospital consultation; a) CV risk consultation and/or Smoking cessation consultation, when applicable; b) Risk prediction algorithms: SCORE2 for patients aged 40 years or more with HDL available; SCORE for patients aged 40 years or more without HDL available; c) Risk prediction algorithms: SCORE2 for patients aged 40 years or more. The enrollment phase includes the OM consultations occurring in the identified companies. The follow-up phase includes the hospital appointments occurring in ULSEDV.

#### Eligibility criteria

2.2.1

The population of this study are the workers of the companies in the municipality of São João da Madeira included in the OM consultation of their company. To be eligible for this study, participants must meet the following criteria:
Age ≥18 and ≤70 yearsWritten informed consent obtained before participating in the study.Participants willing and able to complete the assessments as outlined in this study.Currently employed.

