##### Exclusion criteria

2.2.1.1

Only workers unwilling or unable to complete the assessments will be excluded.

Criteria of follow-up match the criteria for referral to a cardiovascular risk appointment by the Occupational Health physician. These criteria will be based on the Cardiovascular Prevention recommendations from 2021 of the European Society of Cardiology (ESC) and are as described in Table 1, regardless of whether there is a previous history of atherosclerotic disease. The combined use of the SCORE2 and SCORE algorithms reflects data availability in the OM setting: in the case of unavailability of HDL-cholesterol in the OM setting, the legacy SCORE algorithm is used as a pragmatic fallback, consistent with the flexibility allowed under the 2021 ESC guidelines (4, 11, 12).

**Table 1 T1:** Criteria for referral to a cardiovascular risk appointment by the occupational health physician, based on the cardiovascular prevention recommendations from 2021 of the European Society of Cardiology (ESC).

*Markedly elevated single risk factor*
• Total cholesterol >310 mg/dL or LDL cholesterol >190 mg/dL
• Blood pressure >180/110 mmHg
• Moderate or severe chronic kidney disease, defined as eGFR <60 mL/min/1.73 m^2^ (CKD-EPI 2021 creatinine equation)

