#### Data collection

2.2.4

Participants will be assessed in three time points:
at baseline, at their working company by Occupational Safety and Health Technician and by OM doctorat T0, at hospital centre by a medical doctor, for participants referred by the OM doctor based on their CV-risk levelat T12, at hospital centre by a medical doctor, 12 months after T0.Study variables to be used in this study, and related definitions, are described in the following subsections. Table 2 shows the set of data that will be collected and variable features. The main study variables concern demographics, habits, laboratory testing, comorbidities, medications and destination are listed below in more detail.

**Table 2 T2:** Data collection – variables and corresponding features.

Variable	Label	Evaluation period
Inclusion Criteria Check		
consentimento_informado	Signed informed consent	Baseline
avaliacao_possivel	Participant willing and able to complete the assessments	Baseline
Demographics and disease history		
ano_de_nascimento	Birth year	Baseline
sexo	Sex	Baseline
tabagismo_status	Smoking status	Baseline, T0, T12
dieta	Enter Diet Data?^a^	Baseline
sono	On average, how many hours of sleep do you get in a 24-hour period?^b^	Baseline
exercicio_fisico	How many minutes of moderate (or greater) intensity activity per week?^b^	Baseline
drc_moderada_grave	Presence of Moderate or Severe Chronic Kidney Disease	Baseline, T0, T12
dm	Presence of Diabetes Mellitus	Baseline, T0, T12
historia_evento_cv	History of Cardiovascular Event	Baseline, T0, T12
especificacao_eventos_cv	Specification of Cardiovascular Events	Baseline, T0, T12
outros_antecedentes	Other Pathological History	Baseline, T0, T12
Diet Questionnaire		
dieta_porcoes_vegetais_semana	How many servings of vegetables do you consume per week?	Baseline
dieta_porcoes_carne_vermelha_semana	Servings of Red Meat per Week	Baseline
dieta_porcoes_manteiga_creme_semana	How many servings of butter or cream do you consume per week?	Baseline
dieta_porcoes_graos_integrais_dia	How many servings of whole grains do you consume per day?	Baseline
dieta_consumo_fastfood_semana	Times Consuming Fast Food Meals per Week	Baseline
por_es_de_frutas_por_semana	How many servings of fruit do you consume per week?	Baseline
dieta_peixe_semana	How many servings of fish or shellfish/seafood do you consume per week?	Baseline
dieta_feijoes_semana	How many servings of beans do you consume per week?	Baseline

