#### Inclusion criteria check

2.2.5

Inclusion criteria will be checked by Occupational Safety and Health Technician prior to OM appointment.

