### Strengths and limitations

2.4

CARDIOGAP + relies on a low-bureaucracy referral pathway designed for real-world adoption using mandatory occupational health infrastructure to screen a working-age population often missed by primary-care-based cardiovascular screening. In this context, three main limitations should be noted: Possible underestimation of true population-level risk (a “healthy worker effect”) due to restricting enrollment to currently employed individuals (since unemployed, informally employed, retired, and long-term sick-leave workers may carry a higher CV risk burden); Absence of power for a confirmatory test of 12-month risk-factor change (exploratory outcome); Barriers to hospital consultation adherence, which may be limited by shift workers’ difficulty attending hospital appointments, transportation constraints, low risk-perception among asymptomatic individuals, and gaps in OM-hospital communication

However, it should be noted that the low-bureaucracy design partially mitigates all these constraints and limitations, and their impact will be assessed empirically (secondary objectives 1, 2, 3, 7).

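### Read literally, the entry criterion can screen out workers who foresee not attending hospital, which would bias post-referral attendance (endpoint 5) upward by an unknown amount

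*Protocol article*

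**What the plan says.** Section 2.2.1 (Eligibility criteria) requires "Participants willing and able to complete the assessments as outlined in this study". Section 2.2.1.1 makes the converse the sole exclusion: "Only workers unwilling or unable to complete the assessments will be excluded".

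Section 2.2.4 (Data collection) sets out what is assessed: "Participants will be assessed in three time points". These are baseline at the company, then T0 and T12 at the hospital. T0 is for those whom the OM doctor refers on the basis of risk, and T12 follows 12 months later. Table 2 stores the criterion as avaliacao_possivel, labelled "Participant willing and able to complete the assessments" and collected at baseline only. On timing, Section 2.2.5 states: "Inclusion criteria will be checked by Occupational Safety and Health Technician prior to OM appointment".

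Secondary objective 2 is "To assess the rate of hospital CV risk consults that effectively took place after the referral by the OM physician". Endpoint 5 in Table 3 serves it, as the percentage of individuals "who participate in hospital CV risk consultations over all patients referred to hospital consultations".

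Section 2.4 lists four barriers to attending the hospital consultation: shift work, transport, low risk perception in people without symptoms, and communication gaps between OM and hospital. Of the constraints and limitations it names, it says "their impact will be assessed empirically (secondary objectives 1, 2, 3, 7".

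**The concern.** An entry rule that depends on being willing and able to go to hospital selects on the quantity that endpoint 5 later measures. The check comes before risk classification and referral, so a worker who declares a hospital visit impossible would never enter the endpoint 5 denominator. In routine practice that worker could be referred and would count as a non-attender.

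This sits badly with Section 2.4. Two of the barriers named there, shift work and transport, are ones a worker could state at the entry check. Excluding such workers removes part of the effect that the protocol says it will observe. The limitations mention the healthy-worker effect but not this selection.

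Attendance after referral is one of the few direct measures of whether the simplified pathway works, and Section 2.1.3 uses secondary objective 2 for both Reach and Implementation. Reach is expressed over eligible attendees, so workers excluded by this rule leave that denominator too. The Introduction says the pathway should pick up people who do not usually see a primary care physician, a group in which the filter could plausibly matter.

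**Working it through.** **The plan's own figures.** Section 2.2.2 gives a margin of error of 2.2% for a 15% prevalence, 1000 persons and 95% confidence. Check: 1.96 × √(0.15 × 0.85 / 1000) = 0.0221, which agrees. The 150 expected appointments equal 0.15 × 1000 = 150, so every referable worker is assumed to be seen and there is no allowance for non-attendance. Neither figure is affected by this point, and neither supplies an attendance rate.

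**The text, step by step.**
1. The criterion refers to the assessments as the study outlines them (2.2.1), and failing it is the only exclusion (2.2.1.1).
2. The outline has three time points, two of them at the hospital (2.2.4). Nothing in the article limits the criterion to baseline.
3. The check precedes the OM appointment (2.2.5), hence precedes referral.
4. Endpoint 5 divides attenders by those referred, and only enrolled workers can be among them.

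**Direction and size.** Let p be true attendance among all referable workers, f the share of would-be non-attenders removed at entry, and g the share of would-be attenders removed. Then

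observed attendance = p(1 − g) / [p(1 − g) + (1 − p)(1 − f)].

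This exceeds p whenever f > g and equals p when f = g. The values of p, f and g are all assumptions, since the protocol gives none of them.

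With g = 0:

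| True p | f = 10% | f = 25% | f = 50% |
|---|---|---|---|
| 60% | 62.5% (+2.5) | 66.7% (+6.7) | 75.0% (+15.0) |
| 70% | 72.2% (+2.2) | 75.7% (+5.7) | 82.4% (+12.4) |
| 80% | 81.6% (+1.6) | 84.2% (+4.2) | 88.9% (+8.9) |

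Worked case: p = 60%, f = 25% gives 0.60 / (0.60 + 0.40 × 0.75) = 0.60 / 0.90 = 66.7%.

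With some attenders removed as well (p = 60%, f = 25%):
- g = 5%: 0.57 / (0.57 + 0.30) = 65.5%
- g = 25%: 0.45 / (0.45 + 0.30) = 60.0%, so no bias

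**Comparison with sampling error.** With 150 referred, the 95% half-width 1.96 × √(p(1 − p)/150) is 7.8 points at 60%, 7.3 at 70% and 6.4 at 80%. At f = 10% the bias is well inside sampling error. At f = 50% it exceeds it.

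**The case against.** The strongest reply is that the criterion never mentions the hospital. T0 and T12 apply only to referred workers, and Section 2.2.2 expects up to 15% to be referable, so for most workers baseline is the only assessment that applies. The field is collected at baseline only, and nothing tells the technician to ask about hospital visits. The protocol also plainly expects some enrolled workers not to attend, since it lists barriers and divides by all referred. A technician could reasonably read the rule as the ability to complete whatever assessments apply. All of this stands as a reason to doubt how often the rule would bite. It does not settle the wording, which points to a three-visit outline and could be applied differently from one company to the next.

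Foresight is limited too. At the check, workers know neither their risk category nor whether they will be referred. Communication gaps arise only after referral, and low risk perception about a referral not yet made is hard to declare. Only shift and transport problems are readily foreseeable, and those only in part. A reader might infer that the criterion removes the people in whom the barriers operate. The documents support that only for some of the barriers and some of the workers.

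A reader might also infer a very large bias. With p = 60% and f = 75% the formula gives 85.7%, a shift of about 26 points. That requires three quarters of eventual non-attenders to say so before knowing their result, with no would-be attender removed, and nothing in the protocol supports such a share.

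Finally, endpoint 5 is a correct proportion for the workers who are enrolled and referred, and written consent selects willing people in any case. Both points stand. They make this a question of what the rate can be generalised to, with one avoidable layer of selection added to an unavoidable one.

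**Conclusion.** The concern holds as a moderate one. On a literal reading of Sections 2.2.1, 2.2.1.1, 2.2.4 and 2.2.5, workers who foresee that they cannot or will not go to hospital can be excluded before referral. As a measure of the pathway in routine OM practice, endpoint 5 would then be biased upward, which conflicts with the promise in Section 2.4 to assess such barriers empirically.

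The upward direction rests on one assumption: that the rule removes would-be non-attenders more often than would-be attenders. The size is unknown. The range of about +2 to +15 points illustrates assumed attendance of 60 to 80% with 10 to 50% of non-attenders removed, and is not an estimate for this study.

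A reader might go further and conclude that endpoint 5 is invalid, that T12 retention and adherence results are demonstrably inflated, or that the pragmatic claim fails. The documents do not support this. The rate remains valid for enrolled, referred workers, and no effect on retention or adherence can be derived from what is given. Attendance is a secondary, descriptive outcome in a pilot without a formal hypothesis test, and the precision figure in Section 2.2.2 is untouched.

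**What to change.** Limit the criterion in Section 2.2.1, the exclusion in 2.2.1.1 and the label of avaliacao_possivel to the baseline (OM) assessment. Add that foreseen inability or unwillingness to attend T0 or T12 is not a ground for exclusion and, if the worker is referred, counts as non-attendance in endpoint 5.

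If enrolment has begun, report how many workers were excluded under this criterion, with reasons where known. Give a bound beside the main endpoint 5 result: with A attenders among R referred, and E workers excluded because of the hospital visits, report A / (R + qE), where q is the assumed share of E who would have been referred. The risk status of excluded workers may be unknown, because Section 3.2 requires consent before any data are collected. State q openly therefore, for example the planning value of 15%, with q = 100% as the extreme.

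The cost is a wording amendment to the criterion and its matching exclusion, plus one eCRF label. No clinical rule changes. The downside is that reported attendance and T12 retention may be lower. Selection by consent remains and should be acknowledged when the rate is interpreted.
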